### Data management

Results of the assessments will be kept confidential. Participants are allocated a unique identifier to be used when processing and communicating results. Personal details and results will be kept in separate databases and stored in accordance with Australian Psychological Society Ethical Standards and as outlined in the approved ethics application. Any publication of the results will not be published in a manner that would reveal the identity of any participants. The research dataset, de-identified, may be made publicly available.

### Research ethics approval

The project has approval from Monash University Human Research Ethics Committee (Approval Number CF16/2278–2,016,001,131). This ethics approval addresses issues of confidentiality as described above, consent of participants, access to data, ancillary and post-trial care and limitations of dissemination to thesis transcript, journal articles/book chapters, conference papers.

### Statistical analysis

Statistical analysis will be conducted using SPSS version 24 statistical software package. The dependent variables are scores on the two primary outcomes (DASS-21 and the K10), the secondary outcomes (SWLS and FS) and the other mediators (EQ, the MSES-R, the MAIA, and the NAS). The expected outcomes are that the MiCBT group will show significantly changed scores as compared to the wait-list control group, with lower scores on the DASS-21, the K10 and higher scores on the SWLS, FS, the MSES-R, the MAIA, the EQ, and the NAS.

The differential changes in the MiCBT group compared to the control group is the primary focus of the analysis. Analysis will use mixed-model repeated measures (MMRM), the method recommended for clinical trial data [77]. Evidence for the effectiveness of MiCBT will be demonstrated by a significant two-way interaction demonstrating greater change in the outcome measures in the MiCBT group from the control group pre to post intervention. Baseline to follow-up interactions for the MiCBT group will also be examined and changes compared with post intervention data. Results of the trial will be made available to referring clinicians and to participants in the form of a summarized report. Results may be published in journal articles, student thesis and conference presentations.

Intention-to-treat (ITT) analysis will be used because this approach uses all available information. Subjects with incomplete data are not discarded and missing data are not replaced with estimated values. Missing data will be examined and if found to be missing completely at random (MCAR) then the analysis will proceed without replacing missing data with estimated values. If pattern of missingness is not MCAR then multiple imputation will be applied using the strata that defined the non-random missingness.

This is consistent with the CONSORT standard [78]. If data are non-normal, then it will be analyzed using generalized linear MMRM. The mediational impact of pre to post MAIA, MSES, EQ and NAS will be assessed using the Sobel test, a method for measuring indirect effects [79]. The test assesses the significance of the product of the coefficients for treatment-mediator and mediator-outcome effects. A bootstrapped multivariate extension of the Sobel test will be used to examine both the total indirect effect and the individual effect and the effect of each mediator. The first model will comprise: group (MiCBT vs wait-list control) as the independent variable; clinical DASS-21 and K10 measures as the dependent variables; and MAIA (interoceptive awareness), EQ (metacognitive awareness), MSES-R (Emotion Regulation, Distress Tolerance, Equanimity subscales and total) and NAS (equanimity), scales that reveal significant group x time interactions, as mediators. Two time-frames will be tested for changes over the course of the program itself (mediators measured at 4 weeks; outcomes at 8 weeks) and in the longer term (mediators measured at 8 weeks, outcomes at 6 months). The second model will comprise: group (MiCBT vs wait-list control) as the independent variable: psychological wellbeing SWLS and FS measures (measured at 6 months) as the dependent variables; and MSES-R subscales of Taking Responsibility, Social Skills, Interpersonal Effectiveness and total score (measured at 8 weeks), MAIA (interoceptive awareness), EQ (metacognitive awareness), MSES-R (Emotion Regulation, Distress Tolerance, Equanimity subscales and total) and NAS (equanimity) scales that reveal significant group x time interactions, as mediators.

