### Intervention

The MiCBT intervention is adapted from the published protocol [32] with the variation that individual sessions between each group session are not be routinely offered; such sessions are only offered to a participant if a crisis emerges that is deemed too complex to address in a group situation. The MiCBT group will receive the MiCBT treatment in a group format comprising weekly two-hour sessions to groups of 10–15 participants for 8 weeks. The program is delivered by one MiCBT-trained psychologist with 9 years of experience in delivering MiCBT, including twenty-five MiCBT groups. The intervention is administered in a psychology clinic. Participants will be asked to engage in specific mindfulness meditation for an hour each day; two half hour practice sessions and are asked to log their meditation practice hours. Audio instructions for the mindfulness exercises for each session are provided from Cayoun’s (2015) text (used with permission). At the start of each session there is a facilitated group meditation for half an hour which introduces the meditation practice for the following week. There is a review and inquiry process about the experiences of the previous weeks practice and in the second hour of each session there is a psycho-educational component explaining the rationale for the following weeks practice or introducing specific homework designed to apply the skills acquired (e.g. an exposure task to avoided behaviors). Attendance at each session is recorded and non-attenders are followed up. Figure 3 maps the putative processes and outcomes in MiCBT.

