### Sample size

The trial is powered to detect significant differences relevant to the primary outcome. A power analysis (G-power 3.1) for medium effect (Cohen’s d = .5) was conducted with power of .08, and using the conventional significance level (.05), resulting in a desired sample of 102 (51 participants in each group). Consistent with previous studies (e.g. [75]) allowing for a conservatively estimated attrition rate of 20% to follow up, a sample of 120 will be recruited. Based on the projected sample size of 102, power of 0.8, and zero, small, medium or large effect sizes conditions for the indirect effect, the mediation analyses are well-powered to detect a medium beta paths between the independent variable and the mediator and between the mediator and the dependent variable (β = .0.39) using bootstrapping and the Sobel test [76]. Data will be collected using online self-report measures with the Qualtrics platform at the four measurement points; baseline, mid-intervention, post-intervention, and 6-months follow-up.

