### Randomization

All subjects will be allocated an identification number and then randomly allocated to either the MiCBT group or the control group. Randomization is stratified based on the K10 scores (Levels of psychological distress: mild and moderate K10 score < 30; severe, K10 score ≥ 30), antidepressant or mood stabilizer medication (yes/no) and gender. The randomization procedure is conducted using Stata Version 14 SE by a researcher independent from all other aspects of project implementation, including group facilitation and data collection, using random allocation of treatments balanced in blocks. A sequence of treatments (test or control) are randomly permuted in blocks of size 4. Blocks of size 4 were chosen to ensure a balance of treatments in all group sessions, because groups of size 8 could begin as soon as 16 participants are recruited. Allocation is stratified by three stratification variables, each having two values: gender (M/F), antidepressants (Y/N), K10 score (20+/30+). Therefore a randomization schedule is generated for each of the 8 strata: F N 20+; F N 30+; F Y 20+; F Y 30 + M N 20+; M N 30+; M Y 20+; M Y 30+.

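### MiCBT is given in therapy groups and the control condition is not, but the sample size carries no design effect and the stated MMRM has no therapy-group term

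*Protocol article*

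**What the plan says.** All references are to the protocol article.

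- **Intervention.** MiCBT is a group programme, "comprising weekly two-hour sessions to groups of 10–15 participants for 8 weeks", run by one psychologist. Sessions include facilitated group meditation and a shared review of the week's practice.
- **Randomization.** Participants are randomized individually, in permuted blocks of 4 within strata. The block size is justified by the remark that "groups of size 8 could begin as soon as 16 participants are recruited". This group size differs from the one under Intervention.
- **Data collection.** Controls receive usual treatment and complete the measures at the same four time points.
- **Sample size.** The calculation uses an effect size, a power, an alpha and an attrition rate: "d = .5) was conducted with power of .08, and using the conventional significance level (.05". The power is later given as 0.8 ("Based on the projected sample size of 102, power of 0.8"), so the first figure is a misprint. The outcome is a target of 51 per arm, 102 in all, and recruitment is set by "allowing for a conservatively estimated attrition rate of 20% to follow up, a sample of 120 will be recruited". There is no ICC and no design effect.
- **Statistical analysis.** "Analysis will use mixed-model repeated measures (MMRM), the method recommended for clinical trial data [77". Effectiveness rests on a significant arm-by-time interaction, pre to post. Neither this model, its generalized version for non-normal data, nor the mediation models mentions the therapy group.

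**The concern.** This is a partially nested trial: individuals are randomized, one arm is then gathered into small groups for eight weeks, and the other is not. Group members share sessions, discussion and peers, so their changes may be more alike than those of two randomly chosen participants. An MMRM on arm and time handles the correlation between one person's repeated scores. It does not handle correlation between different people in the same group.

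If that correlation exists, the MiCBT mean is less precise than the model reports. The p-value for the arm-by-time interaction, on which effectiveness is to be judged, is then too small, and the planned power is overstated. The stated primary aim is the effectiveness of group delivery, so the grouping is part of what is being tested.

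**Working it through.** **Inputs from the article.** d = 0.5, alpha 0.05 (sidedness not stated), power 0.8, 51 per arm, 120 recruited (60 per arm), therapy groups of m = 10-15 or m = 8. Sixty MiCBT participants make 60/15 = 4 to 60/10 = 6 groups, or 60/8 = 7.5, so 7 or 8, groups of eight.

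**Assumed.** The ICC of pre-to-post change within a therapy group is not in the documents. The range 0.01 to 0.10 is used, with zero as reference.

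**Step 1: reproduce the stated figure.** A two-sample t-test with independent observations (noncentral t), d = 0.5, one-sided alpha 0.05 and power 0.80 gives 51 per arm, 102 in total, with power 0.806. A two-sided test needs 64 per arm, 128 in total. So 102 is an unclustered figure, apparently one-sided.

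**Step 2: put clustering in the MiCBT arm only.**

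Design effect in that arm: DE = 1 + (m − 1) × ICC.
Variance of the arm difference relative to the unclustered value: VR = (DE + 1)/2.

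Example, m = 10 and ICC = 0.05: DE = 1 + 9 × 0.05 = 1.45, and VR = (1.45 + 1)/2 = 1.225. The true standard error is √1.225 = 1.107 times the reported one.

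**Step 3: true type I error of the unadjusted two-sided test**, 2 × [1 − Φ(1.96/√VR)]:

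| m | ICC 0.01 | ICC 0.05 | ICC 0.10 |
|---|---|---|---|
| 8 | VR 1.035, 5.4% | VR 1.175, 7.1% | VR 1.35, 9.2% |
| 10 | VR 1.045, 5.5% | VR 1.225, 7.7% | VR 1.45, 10.4% |
| 12 | VR 1.055, 5.6% | VR 1.275, 8.3% | VR 1.55, 11.5% |
| 15 | VR 1.07, 5.8% | VR 1.35, 9.2% | VR 1.70, 13.3% |

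Simulation of the unadjusted t-test (40,000 trials, 60 per arm) agrees:

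- ICC 0.05: 7.8% with 6 groups of 10, 8.4% with 5 of 12, 9.1% with 4 of 15.
- ICC 0.10: 10.3%, 11.7% and 13.3% for the same layouts.
- ICC 0: 4.8% to 5.1%, so no inflation.

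**Step 4: power on the sample size's own basis** (one-sided, 51 per arm), Φ(0.5 × √(51/(2 × VR)) − 1.645). Here 0.5 × √(51/2) = 2.525.

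- Unclustered: Φ(2.525 − 1.645) = 0.81.
- ICC 0.05, m = 8: Φ(2.525/1.084 − 1.645) = 0.75.
- ICC 0.05, m = 15: Φ(2.525/1.162 − 1.645) = 0.70.
- ICC 0.01: 0.79 to 0.80. ICC 0.10: 0.62 to 0.70.

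To show scale only, keeping the nominal power at ICC 0.05 would take 51 × VR per arm: 60 at m = 8 (120 in total), 63 at m = 10 (126) and 69 at m = 15 (138), against 102.

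**Step 5: does the remedy work with so few groups?** Comparing therapy-group means with individual controls, with Satterthwaite degrees of freedom, gave simulated type I error of about 5% to 6% at ICC 0, 0.05 and 0.10 with 4 to 7 groups.

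**The case against.** **The analysis section is silent rather than wrong.** It names a model family and does not exclude a therapy-group effect. An analysis plan, not shown, could add one, and a journal article condenses. This stands in part: a reader might infer that the trial is committed to treating participants as independent, and the article does not go that far. An analysis plan cannot, however, change the basis of the stated 51 per arm.

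**The ICC is assumed.** This stands. At 0.01 the inflation is negligible and at zero there is none. One psychologist delivers every group from a published protocol, which removes between-therapist variation as a source of correlation. It is tempting to say the error rate is inflated to 9-13%, but that needs an ICC near 0.10, which nothing in the article establishes.

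**Recruitment wave is not a cause.** A reader might add cohort timing to the sources of inflation. The blocks of 4 are meant to balance the arms in each group session, and controls are measured at the same time points, so a wave effect is largely shared by both arms and cancels in their difference. A simulated shared wave gave 4.0-4.6% error, slightly conservative. Only correlation specific to the therapy group inflates it.

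**Power could be made to look worse.** Two-sided at 48 per arm (120 less 20%), power is 0.68 before clustering and 0.55-0.61 at ICC 0.05. The 0.68 already contains two separate matters, the unstated one-sided test and the thin attrition allowance, so those figures should not be charged to clustering.

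**The remedy is imprecise with few groups.** True. With 4 to 7 groups, the between-group variance would be estimated as zero in about 34-36% of trials at ICC 0.05 and 51-54% at ICC 0.01. In those trials the fitted model reduces to the unclustered one. Step 5 used group means, which are not subject to that truncation, so it supports the partially nested approach without guaranteeing the same error rate for every mixed-model fit.

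**Conclusion.** The point holds in conditional form.

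**Sample size and power: wrong as written.** The 51 per arm assumes independent observations in a trial where one arm is treated in groups. On its own apparent one-sided basis, power is about 0.70-0.75 at ICC 0.05, not 0.81.

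**Analysis model: a cheap improvement.** The MMRM as described understates the standard error whenever the within-group ICC of change exceeds zero. True two-sided type I error runs from 5.4% (ICC 0.01, groups of 8) to 13.3% (ICC 0.10, groups of 15).

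These sizes rest on the assumed ICC range, equal group sizes and clustering in the MiCBT arm alone. A design effect applied to both arms would overstate them. Drop-out lowers the number of members contributing data and moves the figures toward the smaller-group rows: a group of 15 losing 20% behaves like one of 12.

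**What to change.** 1. Record each MiCBT participant's therapy group. Session attendance is already recorded, so this is no real extra collection.
2. Prespecify as primary a partially nested MMRM with a random therapy-group effect in the MiCBT arm only, controls treated as ungrouped, and Satterthwaite or Kenward-Roger degrees of freedom. Keep the unclustered MMRM as a sensitivity analysis. Fix this before results are seen, since the Blindness section says the analysis will not be blinded.
3. Restate power, without enrolling more, over an ICC range (for example 0.01, 0.05 and 0.10), using 1 + (m − 1) × ICC in the MiCBT arm and the sidedness actually intended.
4. Reconcile the group sizes given under Intervention and under Randomization, because the design effect depends on them.

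The cost is one extra random term, somewhat wider confidence intervals and, with about 4 to 8 groups, a variance component that is imprecise and often estimated as zero. The report should say so if that happens.

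### The primary group-by-time test is a change-score contrast; a week-8 contrast adjusted for baseline and randomization factors would be more efficient, and the MCAR trigger is not needed

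*Protocol article*

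**What the plan says.** All references are to the protocol article.

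- **Statistical analysis, model:** "Analysis will use mixed-model repeated measures (MMRM), the method recommended for clinical trial data". No covariates are named.
- **Statistical analysis, criterion:** differential change between the arms is the main focus, and "Evidence for the effectiveness of MiCBT will be demonstrated by a significant two-way interaction demonstrating greater change in the outcome measures", from pre to post intervention.
- **Statistical analysis, missing data:** the analysis proceeds without imputation if the data are found to be MCAR. Otherwise, "If pattern of missingness is not MCAR then multiple imputation will be applied using the strata that defined the non-random missingness".
- **Randomization:** "Allocation is stratified by three stratification variables, each having two values: gender (M/F), antidepressants (Y/N), K10 score (20+/30"+).
- **Participant timeline:** the K10 comes from the referring practitioner, before randomization. All other assessments, the DASS-21 among them, are taken after randomization, one week before the program starts.
- **Sample size:** the calculation is "for medium effect (Cohen’s d = .5"), "using the conventional significance level (.05"), "resulting in a desired sample of 102 (51 participants in each group"). Recruitment is set at 120, allowing 20% attrition to follow-up. The section gives no pre-post correlation and does not say on which SD d is standardized.

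**The concern.** The article fixes the form of its primary evidence. Once baseline is a repeated response and the test is the pre-to-post interaction, the efficiency of the test is largely settled. Covariates that do not vary over time, added later as main effects, leave this contrast unchanged when data are complete. The planned test subtracts the whole of each participant's baseline score, although regression to the mean implies that less should be subtracted whenever r is below 1. The price is avoidable variance in a trial of modest size.

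The missing-data rule raises a related problem. A likelihood MMRM is valid under MAR, so a failed MCAR check is no reason to leave it. MCAR can be rejected from data but not established. The rule therefore makes the choice of primary method depend on the observed data without any gain in validity.

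**Working it through.** **1. Inputs.** From Sample size: d = 0.5, alpha 0.05, 51 per arm, 120 recruited, 20% attrition. The article prints "was conducted with power of .08"; this is read as 0.80, since the same section later gives 0.8. After attrition, 120 × 0.80 = 96, or 48 per arm. Assumed, because the article does not give them: r from 0.3 to 0.8, equal variances at the two visits, and d in post-score SD units.

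**2. The article's own figure.** A two-sample t-test with d = 0.5 and one-sided alpha 0.05 needs 51 per arm (power 0.806), which reproduces 102. With a two-sided test, 51 per arm gives 0.706 and 48 per arm gives 0.679. The calculation thus treats the comparison as a plain two-group one, with neither change scores nor adjustment. The results below are two-sided.

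**3. Variances.** With post-score variance s² and n per arm:
- change contrast: 2(1 − r) · s² · (2/n)
- baseline-adjusted contrast: (1 − r²) · s² · (2/n)
- ratio, adjusted to change: (1 − r²) / [2(1 − r)] = (1 + r)/2

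The ratio is below 1 for every r below 1.

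**4. Power.** The standardized effect is 0.5/√(2(1 − r)) for change and 0.5/√(1 − r²) for the adjusted contrast. At r = 0.5 these are 0.5/1.000 = 0.500 and 0.5/0.866 = 0.577. Noncentral-t power, 48 per arm, two-sided 0.05:

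| r (assumed) | variance ratio | change | adjusted |
|---|---|---|---|
| 0.3 | 0.65 | 0.54 | 0.72 |
| 0.5 | 0.75 | 0.68 | 0.80 |
| 0.6 | 0.80 | 0.77 | 0.86 |
| 0.7 | 0.85 | 0.88 | 0.92 |
| 0.8 | 0.90 | 0.97 | 0.98 |

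A simulation at 51 per arm (6,000 trials per setting) agrees with the corresponding calculation: 55.4% against 73.6% at r = 0.3, 69.6% against 82.0% at r = 0.5, and 89.1% against 93.2% at r = 0.7. Below r = 0.5 the change contrast is weaker than comparing week-8 scores alone, because 2(1 − r) then exceeds 1.

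**5. If d is instead in change-score SD units.** The planned test has power 0.68 at 48 per arm whatever r is. The adjusted contrast has standardized effect 0.5 · √(2/(1 + r)): 0.577 at r = 0.5 and 0.527 at r = 0.8, with power 0.80 and 0.72. The direction is the same; the pattern over r is different.

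**6. The post-randomization baseline.** Suppose no treatment effect, and that knowing the allocation raises the control arm's DASS-21 baseline by 0.2 SD without lasting to week 8 (an assumed shift). The change contrast is then biased by the whole shift, 0.20 SD, and the adjusted contrast by about r × 0.2, which is 0.10 SD at r = 0.5. Simulated rejection rates at 51 per arm and r = 0.5 are 17.1% and 8.8%. If the shift lasted in full to week 8, it would cancel from the change contrast, while the adjusted contrast would keep (1 − r) × 0.2 = 0.10 SD. The ordering therefore depends on the shift being transient.

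**The case against.** The planned test is a recognised analysis that matches the stated aim of differential change, and nothing in it is invalid. That stands: the point concerns efficiency. Several stronger readings are tempting, and the article does not support them.

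- **That the test discards baseline.** It does not. It uses baseline, with a slope of 1 where a fitted slope would be more efficient.
- **That the stratification factors are excluded.** The article names no covariates at all, and an article may leave that list to the full plan. The further gain from these factors cannot be computed from the article and is probably small once baseline is in the model, since the K10 band is likely to overlap with the DASS-21.
- **That adjustment is free.** The DASS-21 baseline follows randomization, so adjusting for it may carry some bias, and constraining the arms to a common baseline mean would be unsafe. Obtaining a DASS-21 before allocation would require a change to the assessment schedule.
- **That the gain is always large.** It depends on an unstated r and on the scale of d. It is about 5 points at r = 0.7 and 1 point at r = 0.8.
- **That 48 per arm is the week-8 number.** The 20% is attrition to follow-up, so more participants may be observed at week 8, and an MMRM also uses partial data.
- **That the imputation would omit arm and earlier scores.** The article does not say so, and the imputation model may be specified elsewhere.

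None of this removes the two core points: the stated contrast is less efficient for every r below 1, and the MCAR trigger serves no purpose for a likelihood MMRM.

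**Conclusion.** The point holds as a recommended improvement in efficiency. The stated primary contrast has 1/[(1 + r)/2] times the variance of a baseline-adjusted one, which is 1/0.75 = 1.33 at r = 0.5. On the post-score scale with 48 per arm, the two-sided power lost is about 18 points at r = 0.3, 12 at r = 0.5 and 1 at r = 0.8. The ordering at r below 1 rests on equal variances and a baseline that allocation has not shifted; the sizes rest also on the assumed r and scale of d. The switch of method on an MCAR finding should go, on reasoning that needs no figure. A reader might infer that the planned analysis is wrong or ignores the trial's design; the article supports neither.

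**What to change.** 1. Make the primary test the MiCBT-minus-control contrast at week 8 from an MMRM of post-baseline DASS-21 scores. Adjust for referral K10 (continuous), gender, medication stratum and pre-treatment DASS-21, with covariate effects allowed to differ by visit.
2. Do not constrain the arms to equal baseline means. Report a sensitivity analysis that adjusts only for referral K10, gender and medication stratum, all of which precede randomization.
3. Fit the likelihood MMRM to all randomized participants with data, under MAR, whatever an MCAR check shows. If multiple imputation is kept as a sensitivity analysis, include arm and earlier scores in the imputation model.

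Cost: a few more model terms and a short change of text. All these variables are already collected, and the assessment schedule need not change. The remaining downside is possible bias if knowledge of allocation moved the DASS-21 baseline. Under a transient shift that bias is smaller than in the planned contrast, and the analysis in step 2 does not depend on that baseline.

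### The MCAR check that decides how missing data are handled is not needed for the MMRM, is unreliable at n = 120, and leaves the mediation models without a dependable rule

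*Protocol article*

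**What the plan says.** All of this stands in the protocol article, mainly under Statistical analysis.

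- **Main analysis:** "Analysis will use mixed-model repeated measures (MMRM), the method recommended for clinical trial data". The test of interest is the group-by-time interaction.
- **General statement under intention to treat:** "Subjects with incomplete data are not discarded and missing data are not replaced with estimated values".
- **First branch:** "if found to be missing completely at random (MCAR) then the analysis will proceed without replacing missing data with estimated values".
- **Second branch:** "If pattern of missingness is not MCAR then multiple imputation will be applied using the strata that defined the non-random missingness".
- **Mediation:** the indirect effects "will be assessed using the Sobel test", and "A bootstrapped multivariate extension of the Sobel test will be used to examine both the total indirect effect and the individual effect". One time-frame has "mediators measured at 4 weeks; outcomes at 8 weeks"; the other pairs week-8 mediators with 6-month outcomes. No separate missing-data rule is given.
- **Expected loss (Sample size):** "conservatively estimated attrition rate of 20% to follow up, a sample of 120 will be recruited". It is not split by arm.

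No MCAR check is named. The text does not say whether arm or earlier scores enter the check or the imputation model.

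**The concern.** The rule has three weaknesses.

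1. **The switch has no purpose for the MMRM.** A likelihood MMRM with arm, time and their interaction uses every observed score and is valid under MAR, which is weaker than MCAR. A finding of not MCAR is no reason to change it. The switch only adds a data-dependent fork to the main analysis.
2. **The check cannot carry the decision.** Not rejecting MCAR in 120 people is weak evidence that MCAR holds. Some patterns that matter leave little trace in the usual checks.
3. **The mediation models depend on the rule most.** They are regressions of a later outcome on arm and an earlier mediator. Without imputation, such regressions are ordinarily fitted to people with both values. With imputation, the result depends on what the imputation model contains, and the text names only strata.

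Mechanisms are the secondary aim (Aims and hypotheses). The Methods/design section also relies on the mediation analyses, in the absence of an active control, to help separate specific from general therapy effects. A distorted indirect effect would bear directly on that argument.

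**Working it through.** **The plan's own figures.** The plan attaches no figure to the check, so there is none to reproduce. Its attrition input gives 120 × 0.20 = 24 people lost, about 12 of 60 per arm if the loss is equal. That 20% refers to follow-up; the simulations below apply about 20% at the post-treatment wave, which is an assumption.

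**Step 1: power of a direct dropout-by-arm comparison.** With 60 per arm and two-sided 0.05,

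power = Φ{(|p₁ − p₂| − 1.96·s₀)/s₁}, where s₀ = √[2p̄(1 − p̄)/60] and s₁ = √{[p₁(1 − p₁) + p₂(1 − p₂)]/60}.

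The splits 15% v 25% and 10% v 30% both average 20%, so s₀ = √(0.32/60) = 0.0730 and 1.96·s₀ = 0.1431.

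- 15% v 25%: s₁ = √(0.315/60) = 0.0725; (0.10 − 0.1431)/0.0725 = −0.595; power **0.28**.
- 10% v 30%: s₁ = √(0.300/60) = 0.0707; (0.20 − 0.1431)/0.0707 = 0.804; power **0.79**.

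A moderate imbalance is usually missed; a large one is usually found.

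**Step 2: other checks, by simulation.** Assumed inputs, not in the protocol: 3,000 trials per scenario; 60 per arm; standardised scores at baseline, mid and post; correlations 0.6 (baseline–mid), 0.5 (baseline–post) and 0.7 (mid–post); true effects −0.25 at mid and −0.50 at post; about 20% missing at post.

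| Dropout mechanism | Little-type test without arm | Little-type test with arm | Chi-square by arm |
|---|---|---|---|
| MCAR | 5% | 5% | 4% |
| Arm only, 10% v 30% | 6% | 64% | 80% |
| Depends on mid score in MiCBT arm only (31% v 10%) | 59% | 93% | 83% |
| About 20% per arm, opposite dependence on mid score | 5% | 6.5% | 4.5% |

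The entries are the proportions of trials in which MCAR is rejected. In the last row all three checks perform as if MCAR were true. A check fitted separately within each arm was not tried and should see more.

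**Step 3: the MMRM.** A likelihood estimate from all observed data gave a post effect of −0.50 to −0.51 against a true −0.50 in all four scenarios. The switch therefore gains it nothing under MAR.

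**Step 4: mediation on complete cases.** The indirect effect is a × b, where a is the arm-to-mediator path and b the mediator-to-outcome path.

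- If dropout depends on arm alone, completers are a random subset within each arm. Mediator means and within-arm slopes are unchanged, so a × b is unbiased. Simulation agreed (−0.153 v −0.153).
- If dropout depends on the week-4 outcome score differently by arm, completers' mediator means shift differently in the two arms and path a moves. Inflation ran from **0% to about 25%** as the assumed residual correlation between mediator and outcome rose from 0 to 0.5. A second set of assumed paths gave about 14–23%. These figures are for worse-scoring MiCBT participants leaving; the reverse pattern would shrink the effect.

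**Step 5: the imputation branch.** Mean filling within strata stood in for multiple imputation, to show where the point estimate is drawn (true post effect −0.50).

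| Stratum used | Arm-only dropout | Mid-score dropout, MiCBT only | Opposite dependence |
|---|---|---|---|
| Baseline severity, no arm | −0.39 | −0.51 | −0.56 |
| Arm, no earlier scores | −0.50 | −0.71 | −0.78 |

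Leaving out arm pulls the arms together when dropout depends on arm alone. Leaving out earlier scores exaggerates the difference in these score-dependent scenarios.

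**Reading the steps together.** Arm-only dropout at 10% v 30% is usually flagged by a check that includes arm, yet it does no harm to the complete-case indirect effect. Opposite score-dependence is almost never flagged by the checks tried, yet it can distort that effect.

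**The case against.** The strongest replies are these.

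- **No test is named and arm is not excluded.** A reader might infer that the check cannot detect arm-dependent dropout, or will usually pass. The document does not support that: a check including arm finds 10% v 30% in roughly two-thirds to four-fifths of trials. What stands is low power for moderate imbalance and near-blindness to one specific, constructed pattern.
- **Complete-case mediation is inferred.** The protocol does not state it, and its sentence about not discarding subjects points the other way. What stands is that the first branch forbids imputation and the mediation text offers no other way to keep those people.
- **The imputation model may be sound.** If missingness differs by arm, arm can be read as one of the strata, and detail may sit in a fuller plan. With arm and earlier scores included, imputation would be close to the MMRM. A reader might infer that the second branch is worse than doing nothing; that needs a model the text does not specify.
- **Larger distortions can be produced.** Arm-specific dropout driven by the mediator itself inflated the indirect effect by about 45–60% in one simulation. Nothing in the protocol indicates that pattern. Fitting path a on everyone with a week-4 mediator removed the inflation.
- **The conflict may be only loose wording.** The general sentence could simply describe how an MMRM treats gaps. It carries no condition, though, and the imputation branch contradicts it as written.

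**Conclusion.** The point holds as a low-cost improvement to a stated rule. The paragraph contradicts itself on whether missing values are replaced. The MCAR switch is unnecessary for the MMRM and too weak to govern the other analyses.

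The main result is not shown to be wrong: in the no-imputation branch the MMRM is the analysis one would want. The exposure lies mainly in the mediation models, at about 0–25% inflation of the indirect effect under assumed paths and score-dependent dropout that differs by arm, and none for arm-only dropout. Bias in the imputation branch is conditional on arm or earlier scores being omitted.

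The correlations, effect paths and dropout patterns are assumptions; the protocol gives only n = 120, d = 0.5 and 20% attrition. All of this concerns MAR dropout. Dropout that depends on unobserved scores is covered by neither branch nor by the proposed change.

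**What to change.** - Delete the MCAR check as a decision rule, and remove the conflict over replacing missing values. Missingness can still be described by arm and wave.
- State that all outcomes are analysed by likelihood MMRM on all observed data, under MAR, whatever the missingness pattern.
- For the mediation models, use one approach in every case: multiple imputation with arm, the stratification factors (gender, antidepressant or mood-stabiliser use, K10 level) and all waves of outcomes and mediators in the model, or full-information likelihood.

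The cost is a rewritten paragraph and modest extra work to combine imputation with the bootstrap. Design, recruitment and data collection do not change. The text should acknowledge that neither method protects against dropout related to unobserved scores.
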